## Abstract

**Background:**

The Wake‐Up T2MI Registry is a retrospective cohort study investigating patients with type 2 myocardial infarction (T2MI), acute myocardial injury, and chronic myocardial injury. We aim to explore risk stratification strategies and investigate clinical characteristics, management, and short‐ and long‐term outcomes in this high‐risk, understudied population.

**Methods:**

From 1 January 2009 to 31 December 2010, 2846 patients were identified with T2MI or myocardial injury defined as elevated cardiac troponin I with at least one value above the 99th percentile upper reference limit and coefficient of variation of 10% (>40 ng/L) and meeting our inclusion criteria. Data of at least two serial troponin values will be collected from the electronic health records to differentiate between acute and chronic myocardial injury. The Fourth Universal Definition will be used to classify patients as having (a) T2MI, (b) acute myocardial injury, or (c) chronic myocardial injury during the index hospitalization. Long‐term mortality data will be collected through data linkage with the National Death Index and North Carolina State Vital Statistics.

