Our study has the following objectives: (a) to explore clinical characteristics of patients with T2MI and myocardial injury; (b) to investigate the differences in presentation, stratified by age, sex, and race; (c) to characterize utilization of noninvasive and invasive ischemic evaluation strategies in this population; (d) to determine the rates and burden of obstructive CAD; (e) to determine differences in medical and interventional management of T2MI and myocardial injury; (f) to investigate causes of cardiovascular and noncardiovascular mortality in T2MI and myocardial injury; (g) to identify predictors of in‐hospital, 180‐days, 1‐year, 5‐year, and 7‐year outcomes.

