### Data source

2.1

The Clinical and Translational Science Institute (CTSI) at Wake Forest University Baptist Medical Center (WFUBMC), Winston‐Salem, North Carolina, will serve as the data source and primary organization for this registry. WFUBMC is an academic medical center with 885 licensed beds and is designated as a level I trauma center, serving 24 counties in northwest North Carolina and southwest Virginia. Electronic health records from CTSI will be accessed to study demographics, admission diagnosis, discharge diagnosis, laboratory tests, medications, medical history, procedures, and clinical notes for individuals meeting the specified criteria. Mortality data have been obtained from the National Death Index (NDI) and North Carolina State Vital Statistics from 1 January 2009 to 31 December 2017, and will be utilized for ascertainment of death as an outcome. The study protocol has been approved by the regional Internal Review Board at WFUBMC. This registry is registered in Registry of Patient Registries (RoPR) with RoPR ID number of 43530.

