### Adjudication of T2MI and myocardial injury

2.5

A team of trained study physicians will review all records and utilize the Fourth Universal Definition to classify patients into (a) T2MI, (b) acute myocardial injury, and (c) chronic myocardial injury^2^ (Figure 3). All diagnoses will be adjudicated by two independent adjudicators with disagreements settled by a third adjudicator. All reviewers will have access to all available electronic patient medical records from the index admission described above. To fulfill the biomarker criteria of T2MI, an elevated cTnI of at least >40 ng/L along with an evidence of rise and/or fall of cTnI will be required. If the biomarker criteria is met, clinical conditions with potential to trigger overt ischemia along with any one of the following will be required to be diagnosed as T2MI: (a) symptoms or signs of ischemia recorded in the medical chart; (b) new or presumed new (if unknown baseline) significant ST‐segment/T‐wave changes or new left bundle branch block; (c) development of pathologic Q waves on electrocardiogram; and (d) imaging evidence of new loss of viable myocardium or new regional wall‐motion abnormality.^1^, ^2^ For a diagnosis of acute myocardial injury, an elevated cTnI of at least >40 ng/L along with an evidence of newly detected dynamic rising and/or falling pattern of cTnI and clinical conditions without overt myocardial ischemia will be required. For a diagnosis of chronic myocardial injury, an elevated cTnI of at least >40 ng/L along with stable and unchanging pattern of cTnI and clinical conditions without myocardial ischemia^2^ will be required.

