The Wake‐Up T2MI Registry will generate high‐quality clinical data and its longitudinal design will enable follow‐up of short‐ and long‐term outcomes. Results from this registry may be used to structure future risk‐prediction models aimed at T2MI and myocardial injury. Ultimately, results from our registry will provide data on how to delineate better these entities, determine their cardiovascular prognosis, and potentially develop strategies to mitigate their risk. Presently, we have collected data for 2205 of the 2846 planned subjects; careful adjudication will continue to be undertaken to differentiate T2MI, acute myocardial injury, and chronic myocardial injury. Once study participants are adjudicated into gold standard diagnoses, we might better address questions regarding how baseline characteristics as a function of diagnosis, acute management, and prognosis differ.

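### Class is adjudicated from the whole index stay, where in-hospital death is also counted; deaths before late ischemia evidence are labelled acute injury, which can make T2MI look safer early on

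*Protocol article*

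**What the plan says.** **Classification window.** The Abstract (Methods) says the registry will "classify patients as having (a) T2MI, (b) acute myocardial injury, or (c) chronic myocardial injury during the index hospitalization". Section 2.5 adds: "All reviewers will have access to all available electronic patient medical records from the index admission described above". Neither place gives a time after which evidence stops counting towards the class.

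**Class rules (section 2.5).** For T2MI, "an elevated cTnI of at least >40 ng/L along with an evidence of rise and/or fall of cTnI will be required", plus a triggering condition and any one of four ischemia criteria. The first is "symptoms or signs of ischemia recorded in the medical chart"; the second is a new or presumed new ST/T change or new left bundle branch block. The others are listed as "c) development of pathologic Q waves on electrocardiogram; and (d) imaging evidence of new loss of viable myocardium" or a new wall-motion abnormality. Acute injury needs the same dynamic troponin pattern without overt ischemia. Chronic injury needs a stable pattern without ischemia.

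**Outcomes.** Objective (g) in the Introduction is "to identify predictors of in‐hospital, 180‐days, 1‐year, 5‐year, and 7‐year outcomes". Under section 2.1, death data run "from 1 January 2009 to 31 December 2017, and will be utilized for ascertainment of death as an outcome", so deaths during index stays are covered. The Discussion says that after adjudication "we might better address questions regarding how baseline characteristics as a function of diagnosis, acute management, and prognosis differ".

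**Exclusions (section 2.3).** Patients with a single troponin value, or with data too incomplete to separate T2MI from injury, are left out.

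**The concern.** The exposure (diagnostic class) and the first outcome (in-hospital death) are read from the same stretch of time, and the class rules are asymmetric. Once a troponin rise or fall is on record, T2MI needs a further positive finding, while acute injury is what remains when that finding is absent. Two of the four ischemia criteria, Q-wave development and imaging, can take time to appear. For a patient who depends on one of these, the T2MI label requires living until it is recorded. Within the dynamic-troponin patients, the rule therefore moves deaths in one direction only, from T2MI to acute injury.

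At stake are the between-class comparison of in-hospital and early mortality, and any predictor model for those outcomes that includes the class. Whole-stay classification remains sensible for the descriptive objectives.

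**Working it through.** The article gives no figure for this point, so there is nothing to reproduce. The check asks how large a spurious ratio could be when true risks are equal.

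**Inputs**
- m, true in-hospital death risk, equal in all dynamic-troponin patients: 6%, 12%, 18%. Table 1 reports in-hospital mortality of 6% to 14% for T2MI and 5% to 17.9% for myocardial injury or non-MI groups.
- p, share with qualifying ischemia evidence at presentation: assumed 20% to 30%.
- l, share whose evidence would appear only later, if alive: assumed 5% to 15%.
- f, fraction of deaths in that late group that precede the evidence: assumed 30% to 50%, with milder values below.
- n = 1 − p − l, share who never show evidence.

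**Formulas**
- T2MI risk = [pm + lm(1 − f)] / [p + l(1 − mf)]
- Acute-injury risk = [nm + lmf] / [n + lmf]

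**Worked example:** m = 0.12, p = 0.20, l = 0.10, f = 0.5, n = 0.70
- T2MI: (0.024 + 0.006) / (0.20 + 0.094) = 0.030 / 0.294 = 10.2%
- Acute injury: (0.084 + 0.006) / (0.70 + 0.006) = 0.090 / 0.706 = 12.7%
- Acute-injury:T2MI ratio = 1.25, against a true 1.00

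**Range**
- The full grid above gives 1.06 to 1.39. The top is m = 0.06, p = 0.20, l = 0.15, f = 0.5: 0.0435/0.6545 = 6.65% against 0.0165/0.3455 = 4.78%.
- Milder inputs at m = 0.12, p = 0.30: l = 0.05 with f = 0.10 gives 1.02; l = 0.05 with f = 0.20 gives 1.04; l = 0.02 with f = 0.30 gives 1.02.

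**Carry-over, with time counted from admission.** Take the worked example and give hospital survivors equal later risk. For 37% overall one-year mortality, survival from discharge to one year is 0.63/0.88 = 0.716.
- T2MI: 1 − 0.898 × 0.716 = 35.7%
- Acute injury: 1 − 0.873 × 0.716 = 37.5%
- Ratio 1.05

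At 63% overall mortality the same steps give 1.02.

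**Do the exclusions remove it?** Simulation with m = 0.12, p = 0.25, l = 0.10, exponential death times with mean 6 days, and late evidence uniform on days 0.5 to 6, independent of death time. Whole-stay labels gave a ratio of 1.17 to 1.18 over repeated runs. Dropping every death in the first 12 hours left 1.14 to 1.15, and in the first 24 hours 1.12 to 1.13. Fixing the class at a landmark of 1, 2 or 3 days and counting deaths after it gave 0.99 to 1.01.

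**Direction of the exclusions themselves.** Suppose 5% to 30% of a group's deaths leave the cohort because there was no second troponin or too little data. The acute-injury:T2MI ratio is then 1.04 to 1.40 if only T2MI deaths leave, 0.71 to 0.96 if only acute-injury deaths leave, and 1.00 if the same share leaves both. Example at m = 0.12 and 10%, per 1,000 patients: 12 of 120 deaths leave, giving 108/988 = 10.9% in the depleted group and a ratio of 0.120/0.109 = 1.10 one way or 0.91 the other.

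**The case against.** The other side has a good deal in its favour.

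- **Most T2MI evidence may be early.** Any one criterion suffices. Charted symptoms, or an ST/T change on the first ECG, can qualify at presentation. Only patients with neither, who depend on later Q waves or imaging, can be misrouted. This stands, and it is why the low end of the range matters.
- **Many early deaths are not relabelled.** Those with one troponin or too little data are excluded, and acute injury itself needs a documented rise or fall. This also stands. However, two troponins can exist well before Q waves or imaging, so the exclusions shrink the mechanism without closing it.
- **A reader might infer that everyone who dies early falls into acute injury, so that T2MI is certain to look safer.** The documents do not support that. Some early deaths leave the cohort, and others with no change seen could be called chronic injury. The effect of that selection can run either way.
- **A reader might set the in-hospital ratio beside the 1.19 and 1.27 for injury versus T2MI in Table 1.** Those are 1-year and 4.9-year ratios, so the comparison is not valid. Table 1's in-hospital figures do not point one way: 17.9% against 14%, 9% against 12%, 5% against 6%, and 15% (a non-MI group) against 14%.
- **The full protocol or SAP may set the time origin and adjudicator masking.** That is fair, and their absence from an article is not held against it. A time origin at discharge would remove the death-driven part from later survival, but not from the in-hospital outcome in objective (g).
- **The landmark's clean result is partly built in**, because the simulation draws death and evidence times independently. That is a reason to use it as a sensitivity analysis and not as the main contrast.

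**Conclusion.** The concern holds in a limited form. The text fixes the overlap of windows and the asymmetric rule. It follows that patients with a documented dynamic troponin who die before late-appearing ischemia evidence are labelled acute injury, and this part of the mechanism lowers apparent in-hospital and early mortality in T2MI relative to acute injury.

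The size is not fixed. Under the assumed inputs the spurious in-hospital ratio runs from about 1.02 to 1.39; the upper value is the top of an assumed grid, not a bound. It shrinks with follow-up from admission, to about 1.05 at one year in the worked example. The net direction after the exclusions is also not settled by the documents. These results assume equal true risks, equal later risk among hospital survivors, and values of p, l and f that the article does not give. The point deserves action because the remedy is cheap while adjudication is still under way.

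**What to change.** 1. Add one field to the adjudication form: the date and time at which T2MI evidence first qualified.
2. Keep the whole-stay class for description and for the main analysis.
3. Add a sensitivity analysis of between-class in-hospital and early mortality. Fix the class at a landmark, for example 48 hours after the first cTnI above 40 ng/L with 24-hour and 72-hour variants, and count survival from it. Alternatively, enter T2MI as a time-dependent covariate in the planned Cox model.
4. Report deaths before the landmark for all dynamic-troponin patients together, not by class.

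**Cost.** One field and a small amount of analysis. The Discussion says data are in for 2205 of 2846 patients and that adjudication continues, so the field can still be captured; adding it afterwards would mean re-reading charts. In the landmark analysis early deaths leave the class contrast (about 2% to 5% of patients at 1 to 3 days in the simulation), and T2MI evidenced only after the landmark counts as injury. Both should be stated beside the result.

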**Results:**

We have collected data for a total of 2205 patients as of November 2018. The mean age of the population was 65.6 ± 16.9 years, 48% were men, and 64% were white. Common comorbidities included hypertension (71%), hyperlipidemia (35%), and diabetes mellitus (30%). At presentation, 40% were on aspirin, 38% on β‐blockers, and 30% on statins.

**Conclusion:**

Improved characterization and profiling of this cohort may further efforts to identify evidence‐based strategies to improve cardiovascular outcomes among patients with T2MI and myocardial injury.

ABBREVIATIONSCADcoronary artery diseasecTnIcardiac troponin ICTSIClinical and Translational Science InstituteCVcardiovascularICDInternational Classification of DiseaseREDCapResearch Electronic Data CaptureT1MItype 1 myocardial infarctionT2MItype 2 myocardial infarctionWFUBMCWake Forest University Baptist Medical Center

## INTRODUCTION

1

Myocardial necrosis due to myocardial ischemia is designated as myocardial infarction (MI). Recognizing the heterogeneity inherent to this entity, in 2007 and 2012, the ESC/ACCF/AHA/WHF Task Force for the Universal Definition of MI released expert consensus documents redefining MI into five types.^1^ This classification system was recently further refined with the Fourth Universal Definition of MI.^2^ Type 1 myocardial infarction (T1MI) refers to acute coronary syndrome (ACS) caused by atherosclerotic plaque rupture, ulceration, fissure, or erosion leading to intraluminal thrombus formation and obstructed coronary blood flow. Type 2 myocardial infarction (T2MI) was defined as myocardial ischemia, not due to plaque rupture but secondary to an imbalance between myocardial oxygen demand and/or supply due to an underlying cause.^2^ In defining presence of MI, a critical characteristic is presence of myocardial ischemia; this may be manifested by symptoms, changes on electrocardiography, or evidence for loss of myocardial function. Patients with evidence of elevated troponin with at least one value above the 99th percentile upper reference limit (URL) and 10% coefficient of variation without overt myocardial ischemia are classified as having myocardial injury.^2^ This injury may be acute or chronic, depending on the pattern of cTn elevation and in appropriate clinical contexts.

T2MI and myocardial injury are commonly encountered in clinical practice. In smaller studies, T2MI has been found to be responsible for 2% to 37% of all elevated troponin results in unselected hospitalized patients and 5% to 71% in an unselected emergency department setting.^3^, ^4^, ^5^, ^6^, ^7^ Similarly, myocardial injury has been reported in up to 70% of unselected patients.^8^, ^9^ The heterogeneity in reported frequencies across studies is likely due to differences in biomarkers cut‐offs, selected populations, variation in adjudication processes, and challenges in clinically distinguishing myocardial injury from infarction.

Short‐ and long‐term event rates are higher among patients who experience T2MI compared with patients with T1MI^1^, ^3^, ^4^, ^8^, ^10^, ^11^, ^12^, ^13^, ^14^, ^15^, ^16^, ^17^, ^18^, ^19^, ^20^, ^21^, ^22^, ^23^, ^24^, ^25^, ^26^, ^27^, ^28^ (Table 1). Although the role of underlying coronary artery disease (CAD) and microvascular disease remains unclear, it may play an essential role in influencing outcomes in T2MI.^10^, ^29^ Rates of obstructive CAD in T2MI patients undergoing coronary angiography range from 28% to 78%.^3^, ^8^, ^9^, ^27^ Despite a high prevalence of CAD in these patients, significant disparities exist in medical management of even those with CAD in T2MI or myocardial injury, when compared with those with T1MI^1^, ^3^, ^4^, ^8^, ^9^, ^10^, ^11^, ^12^, ^14^, ^15^, ^19^, ^20^, ^21^, ^22^, ^23^, ^24^, ^25^, ^26^, ^27^ (Table 2).

**Table 1 clc23182-tbl-0001:** Mortality rate of T2MI and myocardial injury in selected studies

Study	N	Mortality of T1MI patients	Mortality of T2MI patients	Mortality of myocardial injury patients	Mortality of T2MI vs T1MI patients	Mortality of myocardial injury vs T1MI patients	Mortality of T2MI vs myocardial injury
Putot et al (2018)^19^	4436 (conventional cTnI ≥10 μg/L)	125 (6.1%) in‐hospital mortality	133 (14%) in‐hospital mortality	260 (17.9%) in‐hospital mortality			
Lambrecht et al (2018)^20^	1568 (cTnI >30 ng/L)	114 of 360 (32%) at 3.2 years. CVD: 68 (61.3%)	74 of 119 (62%) at 3.2 years. CVD: 29 (42.6%)	639 of 1089 (59%) at 3.2 years. CVD: 252 (41.2%)	NA	NA	No difference T2MI vs myocardial injury
Smilowitz et al (2018)^21^	710 (cTnI >0.06 ng/mL)	41 (29.9%) of 137 at 1.8 years. 18 (13%) in‐hospital death	45 (30.8%) of 146 at 1.8 years. 17 (12%) in‐hospital death	52 (29.7%) of 175 at 1.8 years. 16 (9%) in‐hospital			No difference T2MI vs myocardial injury
Arora et al (2018)^22^	1039 (NSTEMI)	12.4% of 775 at 1 year	34.9% of 264 at 1 year		2.80 (2.13‐3.67) RR (95% CI)		
Chapman et al (2018)^10^	2122 (cTnI ≥0.05 μg/L)	430 (37%) at 4.9 years all‐cause. CVD: 253 (22%)	268 (63%) at 4.9 years all‐cause. CVD: 104 (24%)	378 (72%) at 4.9 years all‐Cause. CVD: 145 (28%)	1.51 (1.21‐1.87) RR (95% CI). Adjusted age, sex, renal function, Hb, smoking, diabetes, HTN, CAD, stroke, PVD. 2.15 (1.82‐2.55) unadjusted	2.09 (1.72‐2.55) RR (95% CI). Adjusted age, sex, renal function, Hb, smoking, diabetes, HTN, CAD, stroke, PVD. 2.88 (2.43‐3.40) unadjusted	1.27 (1.08‐1.48) adjusted RR (95% CI). Excess all‐cause mortality of myocardial injury vs T2MI. No difference T2MI vs myocardial injury for CVD
Sandoval et al (2017)^23^	1640 (cTnI value sex specific >99th percentile)	6 (8%) all‐cause mortality at 180 days	18 (13%) all‐cause mortality at 180 days	30 (11%) all‐cause mortality at 180 days			No difference T2MI vs myocardial injury
Cediel et al (2017)^24^	1010 (cTnI >0.039 μg/mL corresponds to 99th percentile URL with coefficient of variation <10%)	74 (19.7%) at 2 years	77 (39.7%) at 2 years	176 (40%) at 2 years	1.41 (1.02‐1.94) HR (95% CI)	1.54 (1.16‐2.04) HR (95% CI)	No difference T2MI vs myocardial injury
Gaggin et al (2017)^26^	1251 (>99th percentile URL or lowest cTn with <10% imprecision)		23.3% per 100 person‐years	3.3% per 100 person‐years in non‐T2MI	2.96 (2.01‐4.36) HR (95% CI) T2MI vs without T2MI		
Sarkisian et al (2016)^11^	1577 (99th percentile URL and coefficient if variation of 10% was >30 ng/L of cTnI)	115 (31%) of 369 at 3.2 years	75 (63%) of 119 at 3.2 years	645 (59%) of 1089 at 3.2 years			1.28 (0.97‐1.65) HR (95% CI). No difference T2MI vs myocardial injury
Smilowitz et al (2016)^25^	475 (>99th percentile URL of cTn)		16 (6%) of all‐cause in‐hospital mortality	10 (5%) of all‐cause in‐hospital mortality			No difference T2MI vs myocardial injury
Shah et al (2015)^12^	2165 (cTnI ≥50 ng/L)	187 (16%) of 1171 at 1 year	134 (37%) of 429 at 1 year	193 (37%) of 522 at 1 year	1.95 (1.61‐2.37) RR (95% CI)	2.36 (1.990‐2.81) RR (95% CI)	1.19 (0.99‐1.42) RR (95% CI). No difference T2MI vs myocardial injury
Baron et al (2015)^13^	19 763 (AMI patients)	13.5% at 1 year	24.7% at 1 year		1.86 (1.66‐2.08) HR (95% CI) unadjusted at 1 year. Adjusted with age, sex, comorbidities, treatment and cTnI level 1.03 (0.86‐1.23)		
Spatz et al (2015)^27^	2082 (AMI patients)	53 (2.2%) at 1 year	3 (2.4%) at 1 year				
Sandoval et al (2014)^4^	1112 (cTnI >34 ng/L corresponds to 99th percentile URL and 10% coefficient of variation)	7.60% death at 180 days	11.4% deaths at 180 days				
Saaby et al (2013, 2014)^9^, ^15^	553 (cTnI >0.03 μg/L)	92 (25.6%) of 360 at 2.1 years	58 (48.7%) of 119 at 2.1 years		2.3 (1.7‐3.3) HR (95% CI) univariable Cox regression analyses		
Stein et al (2014)^14^	2818 (ACS patients)	8.6% at 1 year	23.9% at 1 year				
El‐Haddad (2012)^28^	807 (cTnI ≥1.6 ng/mL)	28 (5.4%) of 512 at 1 year	84 (28.5%) of 295 at 1 year				
Javed et al (2009)^8^	216 (cTnI >0.04 ng/mL)	15 (11%) of 143 in‐hospital mortality	9 (14%) of 64 in‐hospital mortality	67 (15%) of 461 non‐MI group in‐hospital mortality			

Abbreviations: ACS, acute coronary syndrome; AMI, acute myocardial infarction; CAD, coronary artery disease; CI, confident interval; cTnI, cardiac troponin I; cTnT, cardiac troponin T; CVD, cardiovascular death; Hb, hemoglobin; HR, hazard ratio; HTN, hypertension; MI, myocardial infarction; NA, not available; NSTEMI, non‐ST elevation myocardial infarction; PVD, peripheral vascular disease; RR, relative risk; T1MI, type 1 myocardial infarction; T2MI, type 2 myocardial infarction.

**Table 2 clc23182-tbl-0002:** Frequency and CAD prevalence of T2MI and myocardial injury in selected studies

Study	Classification of T2MI and myocardial injury patients	Population	N	Number (%) of T2MI	Number (%) of myocardial injury	Prevalence of CAG and obstructive CAD of T2MI patients	Prevalence of CAG and obstructive CAD of myocardial injury patients	Troponin assay
Putot et al (2018)^19^	Adjudicated by clinician in charge, secondary adjudicated by two cardiologists	Observational prospective study of patients who come to ER university hospital	4436 (conventional cTnI ≥10 μg/L)	947 (21.3%)	1453 (32.8%)	325 (34.3%) had CAG		Siemens Dimension Vista (Siemens Healthineers, Erlangen, Germany)
Arora et al (2018)^22^	Adjudicated by single user	All NSTEMI diagnosed patients of single center study	1039 (NSTEMI)	264 (25.4%) of 1039 NSTEMI patients	NA	68 out of 264 had CAG	NA	Siemens Healthcare Diagnostics
Smilowitz et al (2018)^21^	Classified by consulting and cardiologist and reviewing documentation	Retrospective single center study	710 (cTnI >0.06 ng/mL)	146 (21%)	175 (25%)	19 out of 146 had CAG of which 15 (78.9%) had significant obstruction	19 out of 175 had CAG of which 14 (73.7%) had significant obstruction	Troponin‐Ultra assay (Siemens Healthcare Diagnostics, Erlangen, Germany)
Lambrecht et al (2018)^20^	Adjudicated by three cardiologists	Prospective DEF‐AMI study of all hospitalized patients with elevated cTnI	1568 (cTnI >30 ng/L)	119 (3%) of 1568 patients	1089 (29%) of 1568 patients	28 (23.5%) out of 119 had CAG	57 (5.2%) out of 1089 had CAG	Architect C16000 (Abbott Diagnostics, Abbott Park, III)
Cediel et al (2017)^24^	Adjudicated by two cardiologists according to the Third Universal Definition	Retrospective cohort study in university hospital	1010 (cTnI >0.039 μg/mL corresponds to 99th percentile URL with coefficient of variation <10%)	194 (19.2%) of 1010	440 (43.6%) of 1010	11 out of 194 (5.67%) had CAG	23 out of 440 (5.23%) had CAG	cTnI‐Ultra from Siemens, Advia Centaur
Sandoval et al (2017)^23^	Adjudicated according to Third Universal Definition by two clinicians. Third senior in case of discrepancy	Consecutive unselected patients from emergency department	1640 (cTnI value sex‐specific >99th percentile)	140 (8.5%)	280 (17%)	13 (9%) out of 140 had CAG of which 7 (54%) had significant obstruction	8 (3%) out of 280 had CAG of which 0 had significant obstruction	Hs‐cTnI assays on Abbott ARCHITECT i1000sr or i2000sr analyzers (Abbott, Abbott Park, Ill)
Gaggin et al (2017)^26^	Group of investigators comprising cardiologist. Medical records review based on Third Universal Definition of MI	Single center prospective cohorts (CASABLANCA) study in consecutives patients undergoing coronary and peripheral angiographic procedure	1251 (>99th percentile URL or lowest cTn with <10% imprecision)	152 (12.2%)		61.2% had ≥50% coronary stenosis in ≥2 vessels		Roche Diagnostics Troponin T STAT assay and Roche Cobas e 601 analyzer
Smilowitz et al (2016)^25^	Retrospective review of medical record	Single center retrospective charge review	475 (>99th percentile URL of cTn)	255 (54%)	220 (46%)	20 (8%) had CAG of which 19 had CAD	5 (2%) had CAG of which 4 had CAD	VITROS cTnI ES assay (Ortho‐Clinical Diagnostics, Rochester, NY) or the ST AIA‐PACK 2ng generation (Tosoh Bioscience, Tokyo, Japan)
Sarkisian et al (2016)^11^	Classified by three cardiologists	Prospective study of unselected hospital patients who had a cTnI measured on clinical indication	1577 (cTnI >30 ng/L corresponds to 99th percentile URL and coefficient of variation of 10%)	119 (8%) of total 1577	1089 of (69%) of total 1577 patients with cTnI >0.03 μg/L	28 out of 119 had CAG of which 15 (54%) had significant obstruction	57 out of 1089 had CAG of which 30 (52.6%) had significant obstruction	cTnI Architect c16000. Abbott Diagnostics
Baron et al (2016)^3^	Classified by treating physicians. Included patients with infection	Consecutive patients with MI admitted to cardiac units at 73 hospitals over 3 years	59 394 (AMI patients)	4083 (6.9%)	1549 (2.6%) Unclassified MI	1316 out of 4083 (32.2%) had CAG, of which 52.8% had obstructive CAD	NA	Results are reported for both hs‐cTnT and cTnI, without details
Spatz et al (2015)^27^	Classified by team of five physicians	Prospective cohort study of variation in recovery: Role of gender on outcomes of young AMI patients (VIRGO)	2082 (AMI patients)	123 (5.9%)	NA	35 (28.5%) of 123 had significant obstruction	NA	NA
Shah et al (2015)^12^	Adjudicated diagnoses of T2MI. Adjudicated diagnoses of myocardial injury	Consecutive patients admitted with plasma cTnI values ≥50 ng/L	2165 (cTnI ≥50 ng/L)	429 (26.1%) of total 1643 MI or 19.8% of total 2165 patients	522 (24.1%) of total 2165 patients with cTnI ≥50 ng/L	31 out of 419 (7%) had CAG	19 out of 522 (4%) had CAG	ARCHITECT cTnI assay
Saaby et al (2013, 2014)^9^, ^15^	Adjudicated T2MI diagnoses based on oxygen supply/demand mismatch supplemented by specific clinical standards. cTnI >0.03 μg/L but without overt myocardial ischemia were classified as myocardial injury	Prospective study of unselected hospital patients who had a cTnI measured on clinical indication	553 (cTnI >0.03 μg/L)	144 (26%) of total of 553 MI patients	1408 (71.8%) of total 1961 patients with cTnI >0.03 μg/L	31 out of 144 (21.5%) had CAG of which 17 (54.8%) had significant CAD	56 out of 1089 (5.14%) had CAG of 33 (59.9%) had significant CAD	cTnI Architect c16000. Abbott Diagnostics
Sandoval et al (2014)^4^	Adjudicated by two clinicians based on Universal definition of MI consensus document	Retrospective unselected consecutive patients	1112 (cTnI >34 ng/L corresponds to 99th percentile URL and 10% coefficient of variation)	190 (17%) of 1112 total patients	856 (77%) of total 1112 patients	17 out of 190 had CAG	28 out of 856 had CAG	Ortho‐Clinical Diagnostics (OCD) VITROS cTnI ES assay
Stein et al (2014)^14^	Retrospective validation of T2MI by 2 physicians. Included patients with infection	Prospective collection of patients with ACS	2818 (ACS patients)	127 (4.5%)	NA	36.2% had CAG of which 50% underwent PCI	NA	Details on cTn assays are not reported
Javed et al (2009)^8^	Classified by the interviewing physicians	Prospective evaluation of large cohort	701 (cTnI >0.04 ng/mL)	64 (29.6%)	461 (65.8%)	32 out of 64 (50%) had CAG of which 25 (78%) had significant obstruction	150 out of 461 had CAG of which 78 (52%) had significant obstruction	ADVIA Immunoassay Systems cTnI Ultra assay, Siemens Healthcare Diagnostics

Abbreviations: ACS, acute coronary syndrome; AMI, acute myocardial infarction; CAD, coronary artery disease; CAG, coronary angiography; cTnI, cardiac troponin I; cTnT, cardiac troponin T; MI, myocardial infarction; NA, not available; NSTEMI, non‐ST elevation myocardial infarction; T1MI, type 1 myocardial infarction; T2MI, type 2 myocardial infarction.

Relatively few studies are available comprehensively characterizing the longitudinal profile, medical and interventional management, and short‐ and long‐term clinical prognosis of patients with T2MI or myocardial injury.^26^ There is a lack of consensus on the optimal therapeutic approach to this heterogeneous cohort of patients, including whether they benefit similarly from guideline‐based ACS therapies (as T1MI).^30^ Although select studies have characterized patients with T2MI, patients with myocardial injury have been infrequently studied. Few studies have leveraged linked national and state death records to facilitate more complete mortality estimates.

Our study has the following objectives: (a) to explore clinical characteristics of patients with T2MI and myocardial injury; (b) to investigate the differences in presentation, stratified by age, sex, and race; (c) to characterize utilization of noninvasive and invasive ischemic evaluation strategies in this population; (d) to determine the rates and burden of obstructive CAD; (e) to determine differences in medical and interventional management of T2MI and myocardial injury; (f) to investigate causes of cardiovascular and noncardiovascular mortality in T2MI and myocardial injury; (g) to identify predictors of in‐hospital, 180‐days, 1‐year, 5‐year, and 7‐year outcomes.

